### Intervention

According to ICH-GCP and local regulations, no study procedure can be started until the patient signs the written informed consent. The screening will be carried out after accomplishing the patient's written informed consent. The flow chart is shown in Figure 1. The patients who only meet research criteria will be randomized, otherwise, they will be not.

**Figure 1 F1:**
[figure not shown]
Study flow diagram.

In the withdraw group, the doses of ACEI/ARB/ARNI will be reduced by 50% firstly. The symptoms and signs will be assessed in the following 1 month. The echocardiography and NT-proBNP will be performed to see if they could tolerate a further dose reduction of beta-blockers. Then, the dose of beta-blockers will also be reduced by 50% if the cardiac function of participants is stable. The other drugs of the participants will keep unchanged during the follow-up. In the control group, ACEI/ARB/ARNI, beta-blockers, spironolactone, SGLT2-i, and other drugs will be taken with original doses during the follow up.

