Insights into the pathophysiological mechanisms of heart failure in recovered DCM patients, as well as advances in drugs for heart failure, have enabled the possibility of drug reduction in such patients. First, factors promoting adverse cardiac remodeling in patients with heart failure with recovered ejection fraction have been already suppressed with guideline-directed medications, and one study suggests that there may be a strong attenuation of adverse remodeling factors, such as sympathetic activation and renin angiotensin aldosterone system (RAAS) activation (6). In such circumstance, it may be possible for recDCM patients to reduce the doses of medications for heart failure. Second, with the advent of angiotensin receptor-neprilysin inhibitor (ARNI) and sodium-glucose cotransporter 2 inhibitors (SGLT2-i), patients have experienced significant improvement in the treatment of heart failure compared with previous ones (15). As a consequence, with the application of current novel class of drugs inhibiting cardiac remodeling, the original “ACEI/ARB/ARNI + beta-blockers” doses may have room for diminution. Actually, there are instances in which cardiac function is normalized in a subset of patients with low doses of GDMT for heart failure (14). These indicate that there may be a subset of patients who do not require a target dose to maintain cardiac function, and lower doses may be adequate. Thus, we reasoned that the “ACEI/ARB/ARNI + beta-blockers” halving dose therapy may be non-inferior to original target dose in maintaining cardiac function in recDCM patients.

This is an open-label, randomized controlled, prospective study that will be conducted in patients with recDCM, comparing the safety and efficacy of original target dose and halved dose of “ACEI/ARB/ARNI + beta-blockers.” This will provide essential evidence of whether it is safe and effective to reduce doses of neurohumoral blockades in recDCM patients.

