### Sample size

Regarding the results from clinical trials in heart failure patients, the incidence of cardiac death or heart failure readmission within 12 months is 15–30% with guideline-directed medical therapy. The patients with DCM enrolled in this study have recovered cardiac function and ejection fraction, and TRED-HF study showed a primary endpoint event rate of 0% in such patients with medication doses unchanged in 6 months. Thus, in this study, it is estimated that the primary endpoint rate in control group and in withdraw group is 5 and 7% over 12 months of follow-up. It is estimated that 218 patients would provide the trial with 80% power to show the non-inferiority of halved doses to original doses, a two-sided alpha of 0.05 and a non-inferiority margin of 10% is applied. Considering a loss to follow up rate of 10%, the final sample size is 240. According to the suggestion of the ethical committee, the current study is a pilot study and 50 patients are intended to be included initially, 25 patients per group. After the initial analysis, more patients might be recruited in a further stage of the study.

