## Discussion

The main aim of the present study is to evaluate the efficacy and safety of patients with recDCM who received half-dose neurohumoral blockades and received original dose maintenance therapy, and then by comparing the two doses of treatment, it may be concluded that “ACEI/ARB/ARNI + beta-blockers” halving dose was non-inferior to patients' maintenance dose in maintaining recovered cardiac function in DCM patients. This will provide a significant basis for the choice of whether to reduce dosage or to adhere to original dose maintenance therapy in DCM patients who recovered, to reduce the economic and psychological burden on patients.

Furthermore, this study is only the pilot study of the original research we want to do because the ethics committee needs to protect the interests of patients. Therefore, one of the limitations of this study is the small sample size, and if this study is effective, we will conduct more research.

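### The hypothesis and planned conclusion describe unconditional halving of both drug classes, but the intervention halves beta-blockers only in patients who are stable after the first step

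*Protocol article*

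**What the plan says.** The protocol article describes the experimental regimen in four places.

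- **Intervention (text with Figure 1).** The first step applies to the whole withdraw group: "In the withdraw group, the doses of ACEI/ARB/ARNI will be reduced by 50% firstly". Symptoms and signs are followed for 1 month, and then a check decides on the second step: "The echocardiography and NT-proBNP will be performed to see if they could tolerate a further dose reduction of beta-blockers". The second step is conditional: "Then, the dose of beta-blockers will also be reduced by 50% if the cardiac function of participants is stable".
- **Background and rationale.** The hypothesis names ACEI/ARB/ARNI plus beta-blockers together and says that "halving dose therapy may be non-inferior to original target dose in maintaining cardiac function in recDCM patients". The aim is likewise "comparing the safety and efficacy of original target dose and halved dose of" that combination. Neither has a condition.
- **Discussion.** The conclusion that the trial may reach is, for the same combination, "halving dose was non-inferior to patients' maintenance dose in maintaining recovered cardiac function in DCM patients". Again there is no condition.
- **Sample size.** The power statement promises "80% power to show the non-inferiority of halved doses to original doses". It names no drug class, and its 7% event rate is assigned to the withdraw group.

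The Statistical analysis section analyses all randomized patients by intention to treat, whatever treatment they received.

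**The concern.** A patient whose cardiac function is not judged stable after the first step does not, on a plain reading of the Intervention section, have the beta-blocker halved. That patient remains in the withdraw group for analysis and has followed the protocol exactly. Intention to treat counts the patient there, and a per-protocol set would not remove the patient either. The issue is therefore which question the comparison answers, not adherence.

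The comparison answers a question about a response-guided strategy. The hypothesis and planned conclusion are worded for a fixed regimen. The check spares the second reduction in the patients who looked worst after the first. If the second reduction adds risk for them, a conclusion about halving both classes in all patients would err towards calling it safe. The trial exists to answer that safety question, and the article says that more patients may be recruited after the first 50.

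**Working it through.** **1. The plan's own figure.** Inputs from Sample size: 5% control, 7% withdraw group, margin 10 points, 80% power, 1:1 allocation. Per arm, n = (z_alpha + z_0.80)² × [0.05×0.95 + 0.07×0.93] / (0.10 − 0.02)².

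- One-sided 0.05: (1.645 + 0.842)² × 0.1126 / 0.0064 = 108.8, so 109 per arm and 218 in total. This matches. 218 × 1.10 = 239.8, which gives the stated 240.
- One-sided 0.025, which is what a two-sided 0.05 implies: 138.1, so 139 per arm and 278 in total. This does not match, but it is a separate matter.

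The 7% is set for the withdraw group as randomized, so how the regimen is worded does not change this calculation.

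**2. The sections side by side.**

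| Section | ACEI/ARB/ARNI | Beta-blocker |
|---|---|---|
| Background (hypothesis, aim) | halved | halved, no condition |
| Discussion (planned conclusion) | halved | halved, no condition |
| Intervention | halved first | halved later, only if stable |
| Sample size | class not named | class not named |

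The first two rows agree with each other and differ from the third.

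**3. How large the gap could be.** The documents give neither the share held at step 1 nor the risk of either step, so the following inputs are assumptions. Control risk is 5%. Halving both classes in everyone truly gives 15%, exactly at the margin. There are 109 per arm, and non-inferiority is declared when the upper 95% limit of the risk difference is below 10 points.

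For a strategy excess E:

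P(declare) = Φ[(0.10 − E)/SE − 1.96], with SE = √{[0.05×0.95 + (0.05+E)(0.95−E)]/109}.

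Example, E = 0.090: SE = √[(0.0475 + 0.14×0.86)/109] = 0.0393; 0.010/0.0393 − 1.96 = −1.705; P = 4.4%.

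*Case A: held patients avoid half of their excess.* E = 10 × (1 − s × 0.5) points, where s is the share of the excess that they carry.

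| s | E (points) | P(declare) |
|---|---|---|
| 0 | 10.0 | 2.5% |
| 10% | 9.5 | 3.3% |
| 20% | 9.0 | 4.4% |
| 30% | 8.5 | 5.8% |
| 50% | 7.5 | 9.7% |

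*Case B: held patients return to control risk.* With a fraction f held, E = 10 × (1 − f) points. For f = 10%, 20% and 30%, E is 9, 8 and 7 points and P is 4.4%, 7.5% and 12.3%.

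*At the pilot size of 25 per arm* the standard error is larger and the shift smaller. For E = 9.0, SE = √[(0.0475 + 0.1204)/25] = 0.0820 and P = 3.3%. For E = 7.5, SE = √[(0.0475 + 0.125×0.875)/25] = 0.0792 and P = 5.0%.

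**4. What limits the effect.** The check uses symptoms, signs, echocardiography and NT-proBNP. The Primary endpoint section counts relapse on LVEF, LVEDVi, NT-proBNP or clinical evidence. A patient held because of such worsening may already be a primary event, and withholding step 2 cannot then lower the event count. Understatement needs patients who are judged not stable, are below every relapse threshold, and would later have had an event because of the second reduction. The Intervention section does not tie stability to the relapse thresholds, so such patients are possible, but nothing shows how many there would be.

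**The case against.** The strongest reply is that no estimate or test is wrong. The Intervention section states the stepwise regimen openly, and intention to treat validly estimates the effect of being assigned to it. The unconditional wording stands only in the background and the discussion of a condensed article, and the discussion says no more than that non-inferiority may be concluded. The numerical examples rest on assumed inputs and mostly on 109 per arm, while the current study is a pilot with 25 per arm. The article also does not say what happens to patients who are not stable. The flow diagram is not shown and may do so.

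Most of this stands. It rules out three stronger readings that a reader might infer:

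- *That the power statement is for unconditional halving of both classes and so is wrong.* It names no class, and its 7% belongs to the withdraw group as randomized.
- *That the conclusion has nothing to do with the regimen given.* Patients who are stable at the check do receive both reductions.
- *That the arm's event rate certainly understates the risk.* It does so only under the conditions in step 4 of the working.

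The reply does not remove the conflict itself. Hypothesis and conclusion define what the trial may claim, and as worded they go beyond the regimen that the Intervention section delivers.

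**Conclusion.** The point holds as a mismatch between the regimen named in the hypothesis and planned conclusion and the regimen in the Intervention section. The randomized comparison supports a statement about the stepwise, response-guided strategy. It does not support non-inferiority of halving both classes in every patient with recovered dilated cardiomyopathy. Any bias in that wider claim would run towards safety.

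Its size cannot be determined from the documents and may be small. The range of 3.3% to 12.3% against a nominal 2.5% is an illustration. It assumes a true risk exactly at the margin, 109 per arm, and held patients who are not already events. The change is worth making because it is cheap and affects what may be concluded about safety, but the comparison is not invalid.

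**What to change.** Reconcile the Background and Discussion with the Intervention section, and align the halved-dose wording in Sample size with whichever description is kept. Which regimen is right is a clinical decision and is not proposed here.

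If the stepwise text stands:

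- State the objective, power statement and conclusion for a stepwise strategy: ACEI/ARB/ARNI halved, then beta-blockers halved if cardiac function is stable.
- Make no non-inferiority claim for halving both classes in all patients.
- Beside the primary result, report how many withdraw-group patients received both steps, and whether each primary event fell before or after the second step. This table is descriptive. The groups in it are formed after randomization and should not be compared as if randomized.

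The cost is a narrower claim, some rewording and one table. The table needs the date of the second step to be recorded for each patient. The number of patients and the primary analysis do not change on account of this point.

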### Follow-up and measurement

The participants in this study will be followed up by face-to-face interviews and telephone. First, the demographic data, medical history, physical examination, laboratory tests will be documented as baseline at the beginning of the study. Then, the cardiac function (NYHA classification), 6-min walking test, and Kansas City Cardiomyopathy Questionnaire (KCCQ) score will be evaluated. Patients will be followed up at 1st, 3rd, 6th, and 12th month. Hospitalization for heart failure, heart failure relapse, and other adverse events will be documented. In the last follow-up, the participants will accomplish the examinations such as genes and metabolites and cardiac MRI as appropriate according to the evaluation.

### Patient and public involvement

Patients, their guardians, and public representatives will be informed about the study, and yet they were neither involved development of study questions nor the planning of research design. In the same way, they also neither took part in the recruitment nor the conduct of this study. Results of the study will be published only in peer-reviewed journals, it is no other information on the results of the study that are provided to patients and their guardians.

### Ethics and dissemination

The study protocol has been approved by an ethical committee of Xinqiao hospital, The Army Medical University, Chongqing, China, and was registered at the Chinese Clinical Trial Register (www.chictr.org.cn, ChiCTR2100054051). Patients and their guardians are required to sign written informed consent if the inclusion criteria are met before the beginning of the study, and meanwhile, researchers are supposed to be sure of participants' voluntariness strictly. When there are clear and ongoing contraindications or the patient requests that the study be terminated, the study should be terminated as soon as possible. Participants are free to withdraw at any time. Important modifications to the protocol that may affect the study's progress will be reported to the above-mentioned committee. Results of the study will be disseminated as published articles in peer-reviewed journals.

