### Exclusion criteria

One of the following conditions is met:

1. Uncontrolled hypertension (blood pressure≥160/100 mmHg).2. Valvular heart disease with moderate or greater severity.3. Severe renal insufficiency (estimated glomerular filtration rate (eGFR) <30 ml/min/1.73 m^2^, estimated according to Cockcroft-Gault formula).4. Atrial, supra-ventricular, or ventricular arrhythmia requiring beta-blockers.5. With the implantation of intra-cardiac defibrillator or cardiac resynchronization therapy.6. Ischemic heart disease.7. With severe systemic diseases.8. Diagnosed with secondary cardiomyopathies.

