### Secondary endpoint

Secondary endpoints are major adverse cardiovascular events, including cardiovascular mortality, myocardial infarction, stroke, sustained atrial tachycardia, or ventricular tachycardia.

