### Statistical analysis

Studies will be analyzed using intention-to-treatment and included all patients randomized, regardless of treatment received. Continuous data are expressed as mean ± SD or interquartile range (IQR 25–75). Categorical variables are expressed as a percentage. Continuous variables are compared by an independent sample *t*-test or rank-sum test. The chi-square or Fisher's exact test is used in the analysis of categorical variables. The Cox proportional hazards model was used to analyze and compare the differences in the occurrence of primary endpoint events and key secondary endpoint events within 12 months of follow-up between the trial group and the control group, and the hazard ratio (HR) and 95 % confidence interval will be calculated.

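### The exit rule ends the study, not only the assigned dose strategy, on an ongoing contraindication; this conflicts with intention-to-treat and 12-month follow-up and may cause informative censoring

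*Protocol article*

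**What the plan says.** The protocol article's Ethics and dissemination section has one exit rule with two triggers. It applies when there are "clear and ongoing contraindications or the patient requests that the study be terminated, the study should be terminated as soon as possible". The patient-request trigger shows that this means the study for that patient, not the whole trial. The next sentence deals with consent on its own: "Participants are free to withdraw at any time". The article does not define contraindications, does not limit the rule to one arm, and does not say whether visits or event collection continue afterwards.

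The Statistical analysis section states: "Studies will be analyzed using intention-to-treatment and included all patients randomized, regardless of treatment received". It compares the arms on the primary endpoint with a Cox model and a 95% confidence interval for the hazard ratio. Primary endpoint sets 12 months of follow-up, and Follow-up and measurement places the visits at months 1, 3, 6 and 12.

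**The concern.** An analysis regardless of treatment received is worth something only if outcomes are still collected after treatment changes. The exit rule points the other way: a treatment problem leads to the end of the study for that patient. Because consent withdrawal has its own sentence, the contraindication trigger reaches patients who have not asked to leave.

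A Cox model treats a patient whose follow-up is cut short as having the same later risk as those still under observation. That is doubtful when the reason is clinical. The trial is open-label, so whether a contraindication is clear and ongoing is judged with the arm known. The stated aim is non-inferiority, where events that go unseen mainly in the half-dose arm would favour the desired conclusion. Later secondary events, such as cardiovascular death or stroke, would be missed as well. Outcomes that were never collected cannot be recovered at analysis.

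**Working it through.** **Step 1. The sections side by side**

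| Section | What it requires |
|---|---|
| Statistical analysis | All randomised patients analysed, whatever treatment they took |
| Primary endpoint; Follow-up and measurement | 12 months of follow-up, visits at months 1, 3, 6 and 12 |
| Ethics and dissemination | Study ended as soon as possible on an ongoing contraindication |

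The first two need outcomes to month 12 after a treatment change. The third, as written, stops the study at that point. All three cannot be followed for the same patient.

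**Step 2. The plan's own figures**

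The Sample size section gives 12-month rates of 5% (control) and 7% (half dose), a planned difference of 2 points, and a margin of 10 points. With unpooled variance,

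n per arm = (z for alpha + z for power)² × (0.05×0.95 + 0.07×0.93) / (0.10 − 0.02)².

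- One-sided alpha 0.05: 109 per arm, 218 in total, which matches the plan.
- Two-sided alpha 0.05, as stated: 139 per arm, 278 in total, which does not match.

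That mismatch is a separate matter. It is given here only because both sizes are used in Step 5. The step from 218 to 240 is 218 × 1.1 = 239.8. Recruiting extra patients for loss restores precision but does not remove bias.

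**Step 3. Loss in the half-dose arm only (assumed inputs)**

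The documents give no termination rate and no risk after termination. Assume a share t of the half-dose arm is terminated, a later relapse risk of 30% in those patients, and no loss in control. Observed rate = 7% − t × 30%.

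- t = 5%: 7% − 1.5% = 5.5%; difference from control 0.5 points. Among those not terminated: 5.5/95 = 5.8%.
- t = 10%: 7% − 3.0% = 4.0%; difference −1.0 point. Among those not terminated: 4.0/90 = 4.4%.

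**Step 4. Other patterns of loss (same assumptions)**

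- Same loss in both arms, t = 5%: 5.5% and 3.5%, difference 2.0 points. With t = 10%: 4.0% and 2.0%, difference 2.0 points. The planned difference is unchanged.
- Control only, t = 5%: 7% and 3.5%, difference 3.5 points, which works against non-inferiority.

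**Step 5. What one-sided loss could do to a non-inferiority test (assumed inputs)**

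Take a true half-dose rate of 15%, exactly at the margin, and control at 5%. Let a share f of half-dose events go unseen, with none unseen in control. Probability of declaring non-inferiority = Φ[(0.10 − (0.15(1 − f) − 0.05))/SE − z].

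| f | 109 per arm, one-sided 0.05 | 139 per arm, one-sided 0.025 |
|---|---|---|
| 0 | 5% | 2.5% |
| 10% | 10% | 6% |
| 25% | 27% | 21% |
| 50% | 74% | 74% |

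**Step 6. The pilot**

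With 25 per arm, one patient is 1/25 = 4% of an arm. The Step 3 scenarios amount to 0.05 × 25 × 0.30 = 0.4 and 0.10 × 25 × 0.30 = 0.75 unseen relapses.

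**The case against.** The strongest reply is that this is one loosely worded sentence in an ethics section of a condensed article. It never says that visits or event collection stop. Because withdrawal has its own sentence, the rule could be read as ending only the study intervention, and the full protocol may say so. This stands in part: the end of follow-up is the natural reading of ending the study, but it is inferred. It does not dispose of the point, because the article states a rule, and that rule as worded contradicts its own analysis and follow-up sections.

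A reader might infer that intention-to-treat cannot be carried out. The documents do not support that. Every randomised patient can be analysed in the assigned arm, censored in the Cox model; the harm is incomplete and possibly informative follow-up.

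A reader might also infer that relapses are lost mainly in the half-dose arm. One could argue that "Atrial, supra-ventricular, or ventricular arrhythmia requiring beta-blockers" is an exclusion and a plausible result of halving a beta-blocker, so that half-dose patients would be removed more often. But the exclusion criteria apply at entry and are nowhere made exit criteria. The exit rule covers both arms, and a contraindication to the drugs themselves could also arise on original doses. Nothing says that a control patient with the same event would stay.

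Three further points stand. A relapse that meets the primary endpoint definition at or before termination already counts, and so does an event such as "sustained atrial tachycardia, or ventricular tachycardia" under the secondary endpoint; only later events are exposed. Withdrawal at the patient's request is ordinary and no defect. In the pilot, the assumed scenarios involve less than one unseen relapse, and the non-inferiority sample size belongs to a possible later stage.

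**Conclusion.** The point holds in a limited form. As written, the contraindication trigger ends the study for patients who have not withdrawn consent, and this conflicts with the analysis regardless of treatment received and with follow-up to month 12. The resulting censoring would be health-related and decided with the arm known, so it may be informative.

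The size and direction of any bias cannot be derived from the documents. The fall from 7% to 5.5% or 4.0%, and the rise in false non-inferiority, hold only under the assumed loss shares and later risk with no loss in control. With the same termination share and later risk in both arms, the 2-point difference stays as planned; with heavier loss in control, the bias would run the other way.

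This is a cheap improvement rather than a must-fix. It is worth making because the missing outcomes could not be repaired at analysis, and because the pilot informs whether more patients are recruited.

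**What to change.** Reconcile Ethics and dissemination with Primary endpoint, Statistical analysis, and Follow-up and measurement by separating two events:

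- **Assigned strategy stopped or changed for a contraindication.** The patient stays in the study, attends the remaining planned visits with the same endpoint collection to month 12, and is analysed in the randomised arm.
- **Withdrawal of consent.** Of the two, only this ends follow-up.

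Record the date and reason for each, by arm, so that any imbalance can be seen. If the full protocol already makes this distinction, the article's wording only needs to be aligned with it. The clinical decision on treatment is left untouched.

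The cost is a wording amendment and keeping a few off-strategy patients on visits that are already planned. The downside is that the observed event rate may be slightly less favourable.
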